## 5. Expected Results

MT is a promising treatment for sleep apnea [37,38]. The AirwayGym app [39] is a mobile app for delivering MT using exercises aimed at strengthening the oropharyngeal muscles. Patients are instructed to perform the MT exercises for 20 min daily for at least 3 months. In most MT programs delivered without a smartphone, patients complete the exercises independently at home without feedback from the therapist. The main drawback of this type of MT is low patient adherence, which has been reported to be as low as 10% in some studies [40,41]. Baptista et al. [41] note that most existing mobile health apps for OSA have focused on the diagnosis of snoring or OSA. Smartphone technology can be valuable for treating people with OSA and for conducting MT.

When using this protocol, in addition to reinforcing the need for apps to promote adherence to MT in sleep apnea, we consider it necessary to clinically monitor the anatomical changes that occur during therapy because excess soft tissue surrounding the upper airways can contribute to a narrow and collapsible airway. However, the effects of parapharyngeal fat deposits at different levels on the severity of OSA remain unclear [20,21]. DISE provides accurate vision and evaluation of the site of the collapse of the upper airways under conditions that better approximate natural sleep than with the patient awake [18].

The objective of myofunctional therapy is to improve adherence to CPAP treatment since this monotherapy, despite its high effectiveness, has a low compliance rate.

Another objective set in this therapy is to carry out simple measurements for a better diagnosis and treatment [42].

Ultrasound is a non-invasive, low-risk, and cost-effective imaging modality that can also be used to assess the tongue. Submental ultrasound can be used to characterize the tongue in people with OSA and has shown that increased tongue width and thickness are associated with severe OSA. Ultrasound can also show dynamic movement that characterizes the changes in tongue morphology with activities such as the Müller maneuver [17,18,43]. Yu et al. [19] reported that ultrasound echo intensity increases with increased tongue fat content and strongly correlates with tongue fat measurements in MRI. Given that the IOPI and TDS measure only tongue strength, we consider it important to also measure cervical fat using ultrasound to clinically assess the responses to the AirwayGym app.

### 5.1. Preliminary Results

Additionally, submental ultrasound may be useful to evaluate the effectiveness of MT in sleep apnea. Studies have shown that myofunctional therapy can increase the size and strength of the genioglossus and geniohyoid muscles, which can improve upper airway function and reduce sleep apnea. Submental ultrasound can be used to measure these muscle changes and evaluate the effectiveness of therapy. With 10% of the patients included, there were significant differences (*p* < 0.05) in the initial volume (mm^3^) and lingual thickness (mm) between the control patients and the patients in the groups with moderate–severe sleep apnea. After 3 months of myofunctional therapy, we found a statistically significant improvement in the values of the functional examination with IOPI and the digital spoon and a reduction in lingual thickness (mm) of >15% in the patients studied.

### 5.2. Discussion

The purpose of this protocol is to establish a diagnosis and treatment model for patients with severe apnea. With new technologies, we can carry out personalized and targeted treatment using cost-effective and safe tools for our patients.

There are no publications on the influence of myofunctional therapy on the reduction in cervical fat in patients with sleep apnea and evaluations of obstruction patterns in DISE before and after. Our study will initially be a pilot, with 15 patients in the control group, 15 patients in the TM moderate apnea group, and 15 patients with TM-CPAP severe apnea. Adult obstructive sleep apnea syndrome (OSAS) that begins very early in life has been attributed to the abnormal development of anatomical structures that support the upper airway (UAS). This abnormal development may be related to genetic, epigenetic, environmental interactions, or all factors. There is a continuous interaction between normal orofacial development and orofacial motor functions, with the involvement of the sensorimotor innervation of the orofacial region, particularly the tongue and mouth. Myofunctional therapy is a theoretically effective treatment in patients with moderate OSAHS and an adjuvant treatment to continuous positive airway pressure therapy, but more scientific evidence is needed to establish its effectiveness. The hypothesis of our work is to study the sensorimotor function of the tongue (apraxia, strength, and stereognosis) before and after oropharyngeal exercises performed with an application based on proprioceptive rehabilitation called Airway Gym^®^ and to see if, in patients with sleep respiratory disorders that present abnormalities in the sensorimotor function of the UAS, there is a significant improvement after myofunctional therapy. Determining the knowledge of the fatty and muscular components can be decisive in the choice of pharyngoplasty techniques, in multilevel surgery, and as a possible predictor of response or failure to MT since, currently, the influence that MT can have on reducing cervical fat is unknown.

Given that the aforementioned tools only measure strength, we consider the previous study of cervical fat using ultrasound and its response to TM relevant in the study of collapse patterns during DISE.

Submental ultrasound is a non-invasive technique used to evaluate the size of the genioglossus and geniohyoid muscles, which are important in keeping the upper airway open during sleep. These muscles are located at the bottom of the jaw and are inserted into the tongue and larynx.

In the setting of OSA, submental ultrasound can be used to determine whether the size of these muscles is adequate to keep the upper airway open during sleep. If these muscles are small or weakened, there may be an increased risk of airway obstruction and sleep apnea [44]. Due to MT ameliorating OSA and sensorimotor deficit in selected patients, all clinical information obtained from the muscle pattern can be a useful tool for more accurate future therapeutic decisions [11,45].

We are interested in comparing the results obtained from the anthropometric characteristics of our patients with other populations to verify if there are significant differences between them [46,47].

Despite the strengths of this pilot study mentioned above, we note several limitations. First, the number of participants is small. The number of patients in the control group is low because we found significant differences in the therapy group early during this study. We therefore decided not to enroll more patients in the control group because of the difficulties experienced by patients with severe OSAHS not given appropriate therapy.

There is no blinding since it is a diagnostic protocol. Mood disorders are not analyzed since the exclusion criteria include patients with serious illnesses or those taking treatments that affect apnea.

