### 2.2. Study Groups

The control group will include patients with recent moderate–severe sleep apnea (1–3 months) undergoing treatment with continuous positive airway pressure (CPAP) therapy. An initial ultrasound measurement of the tongue genioglossus fat will be made and 3 months after inclusion in this study.

The MT group will include patients with moderate apnea. MT exercises alone, once a day for 3 months, will be performed exclusively via the AirwayGym app. An initial ultrasound measurement and drug-induced sleep endoscopy (DISE) will be performed with repeated control at 3 months.

In the MT-CPAP severe apnea group, patients will use CPAP at night, measuring the number of hours they use it at night. A new sleep study will be performed at 3 months. An initial ultrasound measurement and DISE will be made with control at 3 months (Figure 1).

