### 4.1. Sample Size

Calculation of sample size

No studies have reported on the influence of MT on the reduction in cervical fat in patients with sleep apnea and evaluations of obstruction patterns in DISE before and after. Our study will initially be a pilot study, with 15 patients in the control group, 15 patients in the moderate MT apnea group, and 15 patients with MT-CPAP severe apnea.

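### The plan states 15 controls, but the limitations say control enrolment was ended after early results in the therapy group, with no rule described and a reason that conflicts with the group definition

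*Protocol article*

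**What the plan says.** Section 4.1 of the protocol article fixes the size: "Our study will initially be a pilot study, with 15 patients in the control group, 15 patients in the moderate MT apnea group", with 15 more in the MT-CPAP group. The Discussion (5.2) repeats it, still in the future tense: "Our study will initially be a pilot, with 15 patients in the control group".

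The limitations at the end of 5.2 say something else: "The number of patients in the control group is low because we found significant differences in the therapy group early during this study". The next sentence gives the consequence, "We therefore decided not to enroll more patients in the control group", and adds a clinical reason: the hardship of severe patients left without suitable treatment.

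Section 2.2 defines the controls as "patients with recent moderate–severe sleep apnea (1–3 months) undergoing treatment with continuous positive airway pressure (CPAP) therapy".

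The early data are in section 5.1: "With 10% of the patients included, there were significant differences" in initial tongue volume and thickness between controls and the apnea groups. A separate sentence reports significant improvement in the two tongue-strength measures after 3 months of MT, and a fall of more than 15% in tongue thickness. It gives no number of patients and no control result.

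Section 2 calls the study a non-randomised pilot, and the limitations say that it is not blinded. The statistical paragraph that closes section 4.3 lists ordinary two-group and multi-group tests. It mentions no early look.

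**The concern.** All of these statements are current text. One part of the article plans 15 controls. Another says the control number is low and was held there after results had been seen. The reader cannot tell how many controls the comparisons will rest on.

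The logic of the decision is also weak. Without randomisation or blinding, a before-after change under MT mixes any treatment effect with practice on the strength tests, regression to the mean and measurement drift. The control group is the only one without MT, so it is the only concurrent check on these. An early improvement in the treated patients makes that check more necessary.

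At stake are the precision of every comparison with control and the weight a reader can give to claims of significance that preceded the decision.

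**Working it through.** **1. The passages side by side**

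| Point | One place | Another place |
|---|---|---|
| Control number | 15 (4.1, repeated in 5.2) | Low, enrolment ended (5.2, limitations) |
| Reason for ending enrolment | Early differences in the therapy group (5.2) | No early look or rule described (4.1, 4.3) |
| Treatment of controls | CPAP (2.2) | Reason given refers to severe patients without suitable therapy (5.2) |

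**2. How much early data is described**

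Planned total: 15 + 15 + 15 = 45. Ten per cent is 0.10 × 45 = 4.5, so 4 or 5 patients over three groups. The between-group result reported at that point concerns initial volume and thickness. That is a baseline difference: it bears on whether the groups are comparable and says nothing about the effect of MT. The 3-month sentence has no n and is not tied to the 10%.

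**3. What fewer controls would cost**

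The article gives no effect size, SD or power, so there is no planned figure to reproduce. The following is illustrative. Assumptions: two-sided alpha 0.05, common SD of 1, one MT group of 15 against n_c controls, two-sample t-test. The n_c values are assumed, because the achieved number is not given.

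- Standard error of the difference, in SD units: SE = √(1/15 + 1/n_c)
- 95% CI half-width = t(0.975; 13 + n_c) × SE
- Detectable difference: the d at which the noncentral t distribution, with 13 + n_c degrees of freedom and noncentrality d/SE, gives 80% power
- Last column: power for the 1.06 SD difference that 15 against 15 detects with 80% power

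| n_c | SE | SE relative to 15 v 15 | t | CI half-width (SD) | Detectable d, 80% power | Power at 1.06 SD |
|---|---|---|---|---|---|---|
| 15 | 0.365 | 1.00 | 2.048 | 0.75 | 1.06 | 80% |
| 10 | 0.408 | 1.12 | 2.069 | 0.84 | 1.19 | 70% |
| 8 | 0.438 | 1.20 | 2.080 | 0.91 | 1.29 | 64% |
| 5 | 0.516 | 1.41 | 2.101 | 1.09 | 1.53 | 49% |
| 3 | 0.632 | 1.73 | 2.120 | 1.34 | 1.89 | 35% |

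Example for n_c = 5: SE = √(0.0667 + 0.2000) = 0.516, and 0.516/0.365 = 1.41.

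**4. Does the decision inflate the error of the final test?**

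Simulation under no effect, 200,000 runs per setting, final two-sample t-test at 0.05:

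- Controls stopped because the first 3, 5 or 8 MT patients improved significantly on their own: final error 4.9%, 4.9% and 4.9% (rounded).
- Controls stopped because an early MT-versus-control test at 2 to 8 per group was significant, which the article does not describe: final error 5.5% to 6.0%.

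On either reading, the overall error of the final test stays close to nominal.

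**The case against.** The strongest reply is that this is a self-described pilot with no power claim, that its groups are defined partly by severity so control comparisons are confounded at any size, and that the low control number is openly listed as a limitation. All of that is true. It lowers what the comparison could ever show. It does not settle which control number applies, and naming a limitation does not remove the 15 that still stands in two places.

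A second reply is that the control number may be low only relative to 30 MT patients, with 15 controls enrolled as planned. The text allows this. A shortfall is the more natural reading, but it is not stated, so the article cannot be said to have missed its 15.

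Three stronger readings are tempting, and the document does not support them:

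- **An unplanned interim analysis of MT against control.** The limitations speak of differences in the therapy group, and the only between-group result in 5.1 is at baseline. No early outcome comparison with control is shown to have triggered the decision.
- **A materially inflated type I error.** This depends on the reading above, and the simulation shows the final test near 5% in any case.
- **Significance was impossible with so few patients.** That holds for rank tests at 4 or 5 patients, but section 4.3 names the t-test first, and a t-test can fall below 0.05 with very few observations. The 3-month result also has no stated n.

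The authors' clinical reason deserves respect as a motive. It still does not fit the group described in section 2.2, and the article must resolve that.

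**Conclusion.** The point holds in this form: the article gives a control number of 15, and also says that control enrolment was ended, with a low number, after early results had been seen. It describes no look or rule for this, and the reason it gives conflicts with its own definition of the control group. The early results it reports cannot carry such a decision: one is a baseline difference in about 4 or 5 patients, the other a change without n or comparator.

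The size of the loss is unknown because the achieved number is not given. Over an assumed range of 10 down to 3 controls against 15 MT patients, the detectable difference goes from 1.06 SD to between 1.19 and 1.89 SD, and the standard error rises by 12% to 73%. If 15 controls were in fact enrolled, there is no loss of precision, and what remains is the contradiction and the undisclosed basis of the decision. That the look was unplanned rests on this article alone, since the full protocol and analysis plan are not shown.

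**What to change.** 1. Reconcile sections 2.2, 4.1, 5.1 and 5.2 on the number of controls, their treatment and the reason for ending their enrolment.
2. If fewer than 15 controls were enrolled, replace 15 by the actual number in 4.1 and 5.2, with the precision it gives (expected confidence interval width or detectable difference). If 15 were enrolled, say so and reword the limitation.
3. Remove early significance as a reason for closing control enrolment. Disclose that results were looked at before the decision, which results, and in how many patients.
4. Report all comparisons with control as descriptive estimates with 95% confidence intervals, without claims of significance.
5. Withdraw the early significance statements in 5.1, or label them exploratory and give the n behind each.

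The cost is a text amendment, possibly a less favourable stated control number, and weaker claims. No additional patients are required.

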## 2. Experimental Design

This is a nonsponsored prospective, non-randomized pilot study coordinated by the Pulmonology, Anesthesiology, and Otolaryngology Departments of Quirónsalud Marbella Hospital and Campo de Gibraltar Hospital, Andalucia, Spain. This study has been registered (ISRCTN92645461) and approved by the local ethics committee (AWGAP20232).

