### 2.3. Objectives

-To evaluate the influence of MT on the reduction in cervical fat and the improvement of ultrasound parameters in sleep apnea.-To measure different parameters related to the function and size of the genioglossus and geniohyoid muscles to evaluate the presence and severity of sleep apnea, as well as the effectiveness of myofunctional therapy in improving the function of these muscles.-To determine whether performing a neck ultrasound is relevant for the indication of TM in sleep apnea.-To evaluate whether performing ultrasound and DISE modify the indication of surgical techniques compared with if we only performed DISE.-To evaluate the adherence to CPAP and MT.

The hypothesis of our work is based on determining whether knowledge of the fatty and muscular components can be decisive in the choice of pharyngoplasty techniques, in multilevel surgery, and as a possible predictor of response or failure to MT since, currently, the influence that TM can have on reducing cervical fat is unknown.

Given that the aforementioned tools only measure strength, we consider the previous study of cervical fat using ultrasound and its response to TM relevant in the study of collapse patterns during DISE.

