DISE is performed in an operating room using a flexible endoscope and standard anesthetic monitoring of the oxygen saturation, electrocardiogram, and blood pressure. Although not mandatory, recording media (with or without audio) and playback equipment are recommended. DISE video sequences can be used for educational and research purposes or to inform patients about their test results. In our setting, an otolaryngologist will perform the endoscopic procedure, and an anesthesiologist will monitor the patients and observe their responses to medication and the procedure. Basic and advanced maneuvers (e.g., chin lift, jaw thrust, and head rotation) will be performed during DISE. The VOTE classification system is used to record the results [27,29,30,31] (Figure 3).

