The distribution of visits to the center will be as follows:Pulmonology visit: Patients will be diagnosed with OSA in a pulmonology laboratory via an initial sleep study, which includes the measurement of baseline AHI, the nocturnal desaturation index, and the lowest oxygen saturation levels during the night.Otorhinolaryngology visit: Patients will be assessed by the otorhinolaryngologist, who will evaluate the anatomy and functionality of the upper airways using DISE and measure tongue strength with the IOPI and TDS. The AirwayGym app is recommended for patients with oropharyngeal hypotonia.Ultrasound visit: A neck ultrasound will be performed to measure tongue thickness (mm), height (mm), volume (cm^3^), and distance between the lingual arteries (mm) before DISE and at the start of treatment modulation with the app (Figure 4 and Figure 5).Monthly telemedicine follow-up: During the 3-month study period, all patients in the three groups will be monitored for adherence and incidents related to the prescribed treatment with the AirwayGym app.Three-month follow-up: All variables evaluated during the initial visit will be measured again after three months. The ultrasound visit is an evaluation added to this previously published protocol (Tongue +) [36]. A submental ultrasound will be performed in the context of sleep apnea.

The Kolmogorov–Smirnov test will be used for the distribution of quantitative variables. The chi-square test or Fisher test will be used as necessary for the study of categorical variables. Student’s *t*-test or ANOVA (for two or more samples) will be used to study the differences between quantitative variables.

Non-parametric tests (Mann–Whitney or Kruskal–Wallis) will be used if the variables to be analyzed do not follow a normal distribution. The level of statistical significance will be set at *p* < 0.

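### Blinding is waived because the study is called a diagnostic protocol; reader-dependent outcomes are left open to bias and no DISE-only surgical indication is secured for objective 4

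*Protocol article*

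**What the plan says.** Section 5.2 (Discussion) lists the absence of masking among the limitations, with a single reason: "There is no blinding since it is a diagnostic protocol".

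Other parts of the protocol article bear on that reason:

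- Section 2.2 defines a CPAP control group, a myofunctional therapy (MT) group and an MT-CPAP group.
- The first objective in section 2.3 is a treatment effect: "To evaluate the influence of MT on the reduction in cervical fat and the improvement of ultrasound parameters in sleep apnea".
- Section 6 describes the work as both diagnostic and therapeutic, and says that ultrasound results need a trained and experienced interpreter.
- The outcomes in section 4.2 include VOTE grading in DISE before and after, and ultrasound echo intensity, tongue height and tongue width. Section 4.3 adds thickness, volume and the distance between the lingual arteries.
- On DISE recording, section 4.2 says: "Although not mandatory, recording media (with or without audio) and playback equipment are recommended".

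The fourth objective in section 2.3 is a comparison of diagnostic strategies: "To evaluate whether performing ultrasound and DISE modify the indication of surgical techniques compared with if we only performed DISE". In section 4.3 the neck ultrasound is done "before DISE and at the start of treatment modulation with the app". The same list of visits places DISE with the otorhinolaryngologist, "who will evaluate the anatomy and functionality of the upper airways using DISE and measure tongue strength with the IOPI and TDS", in a visit listed ahead of the ultrasound visit.

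**The concern.** The stated reason conflicts with the design. A study that compares treatment groups and asks whether MT changes ultrasound parameters makes a claim about treatment, and the person who places the measurement or assigns the grade can influence it. A purely diagnostic aim would not help either: to compare two tests, each should be read without knowledge of the other. Patients cannot be masked to doing exercises, but the readers of stored images and videos can be.

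Two things are at stake. First, if a reader knows the group and the visit, a small unconscious shift at 3 months cannot be told apart from an effect of MT. Expectation is a real possibility here: section 5.2 says that control enrolment was stopped because differences in the therapy group were seen early. Secondly, objective 4 needs a surgical indication formed from DISE alone. If the otolaryngologist already has the ultrasound result, that comparator is contaminated.

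**Working it through.** **Comparison of passages.**

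1. *Reason against design.* Section 5.2 relies on a diagnostic purpose. Sections 2.2, 2.3 and 6 describe treatment groups, a treatment-effect objective and a therapeutic purpose. Section 5.1 already reports a reduction in lingual thickness of more than 15% after MT. The reason does not cover the study described.
2. *Exposed outcomes.* Ultrasound dimensions, echo intensity and VOTE depend on a reader. The IOPI and digital spoon give instrument readings and are much less exposed. No masking of readers to group, visit or the other test is described, and DISE recording is optional, so a later masked reading is not guaranteed.
3. *Objective 4.* The only explicit order is ultrasound before DISE, although the visit list puts the visit containing DISE first. In neither order is a step described at which the indication from DISE alone is written down.

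**Illustration of size.** The article gives no figure for reader error, so there is none to reproduce.

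Inputs:
- n = 15 per group (section 4.1).
- Two-sided alpha 0.05, assumed. The level in section 4.3 is cut off in the text; section 5.1 uses 0.05.
- SD of the percentage change in thickness: 8%, assumed, range 5–12%.
- Reader shift b at 3 months: 3% or 5%, assumed, in one group only. The larger value is a third of the reported 15% (5/15).
- No true effect.

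Formulas (noncentral t):
- Between two groups: df = 2 × 15 − 2 = 28, noncentrality = (b/SD) × √(15/2), critical value 2.048.
- Within one group: df = 15 − 1 = 14, noncentrality = (b/SD) × √15, critical value 2.145.

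For b = 3 and SD = 8, b/SD = 0.375. The noncentrality is 0.375 × 2.739 = 1.03 between groups and 0.375 × 3.873 = 1.45 within a group.

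Probability of p<0.05 with no true effect:

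| Shift | SD | Between groups | Within group |
|---|---|---|---|
| 3% | 5% | 35.5% | 58.0% |
| 3% | 8% | 16.8% | 27.3% |
| 3% | 12% | 10.1% | 14.7% |
| 5% | 5% | 75.3% | 94.9% |
| 5% | 8% | 38.0% | 61.5% |
| 5% | 12% | 19.7% | 32.4% |

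For a shift of 1% the between-group figure is 6.3% at SD 8% (5.6–8.3% over the range of SD), close to the nominal 5%.

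**The case against.** The strongest reply has five parts.

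- *The limitation is disclosed, in a small pilot.* That is true, so nothing is concealed. But disclosure with a reason that does not apply is not mitigation.
- *Objective 4 may still be answerable.* A reader might infer that a DISE-only indication is never obtained, or that no patient will have one. The document does not support that. Scanning first fixes when images are acquired, not when the result reaches the otolaryngologist, and the order is itself ambiguous. The variable list in section 4.2 is not exhaustive either: it omits lingual volume, the sleep questionnaires and CPAP hours, all mentioned elsewhere. The absence of surgical indication from that list in a condensed article does not show that it goes unrecorded. What stands is that no step is described that secures it.
- *Not every outcome is affected.* A reader might infer that all outcomes are compromised, or that an effect on VOTE is already claimed. Neither follows. The IOPI and digital spoon are instrument readings, and section 5.1 reports post-treatment change only in these and in lingual thickness.
- *The size rests on assumptions.* This stands. The SD and the shifts come from no document. Section 4.3 names tests that compare groups, for which the rates are lower than for a within-group test, and a shift common to both groups would cancel.
- *Masked re-reading is only a partial remedy.* This also stands. Probe position, pressure and choice of frame act at acquisition, and images from patients already studied may not exist.

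**Conclusion.** The concern holds in this form: the reason given for having no masking is contradicted by the study's own groups, objective and description; reader-dependent ultrasound and VOTE outcomes are left open to measurement bias; and an uncontaminated DISE-only comparator for objective 4 is not secured. It should be corrected.

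The consequence could be material but cannot be fixed from the document. Under the assumptions above, a 3% shift in one group gives a false-positive rate of 17% (10–35%) between groups or 27% (15–58%) within a group. A 5% shift gives 38% (20–75%) or 62% (32–95%). The ranges reflect SD only. These figures show sensitivity to bias; they are not evidence that such bias occurred.

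**What to change.** 1. Require storage of ultrasound images and DISE videos for all remaining patients.
2. Have the same reader measure and grade coded files in random order with group and visit hidden, including existing files where available.
3. Withhold the ultrasound result until the surgical indication from DISE alone has been recorded. Record the indication again after disclosure, and report the proportion changed with an exact confidence interval.
4. Reconcile the order of ultrasound and DISE in section 4.3.
5. Replace the diagnostic-protocol reason in section 5.2 with a statement that patients and operators are unblinded and readers are masked.

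The cost is file storage and coding, later reading and an added form entry for the indication before and after disclosure; no extra reader or procedure is needed. Research readings become available later, acquisition bias remains, and earlier patients without stored files must be reported as read unmasked.
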